#### Outcome

The details of items to be measured and time points for data collection are shown in Table 2.

**Table 2 T2:** Trial schedule.

Study phase		Screening period	Intervention period (12 weeks)		Follow-up period (24 weeks)	
Visit		V1	V2	V3	V4	V5
		−3–0 days	Week 4 ± 2 days	Week 12 ± 3 days	Week 24 ± 5 days	Week 36 ± 7 days
Inclusion/exclusion criteria		×				
Informed consent		×				
Random allocation		×				
Baseline data collection	Demographic information	×				
	Medical history	×				
	Past medical history, allergies	×				
Safety evaluation	Vital signs	×	×	×		
	Blood, urine, and stool routines	×	×	×		
	Liver and renal function	×	×	×		
	Blood lipids	×	×	×		
	coagulation function	×	×	×		
	Adverse events		×	×	×	×
Outcome evaluation	CPET	×		×		
	Composite endpoint events		×	×	×	×
	Other indicators in CPET	×		×		
	SAQ, SF-12	×	×	×	×	×
	TCM syndrome scale	×	×	×	×	×
	PHQ-9, GAD-7	×	×	×	×	×
	echocardiography	×		×		
	electrocardiogram	×		×		
	Metabolomics analyses	×		×		
Drug distribution		×	×			
Recovery drug			×	×		
Record drug combination			×	×	×	×
Evaluate compliance				×		

CPET, cardiopulmonary exercise testing; SAQ, seattle angina questionnaire; SF-12, 12 items of short form health survey questionnaire; TCM, traditional Chinese medicine; PHQ-9, patient health questionnaire-9; GAD-7, generalized anxiety disorder-7.

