#### The primary and secondary outcomes

The primary outcome is the improvement of METs in CPET. METs are an important indicator for evaluating aerobic metabolism and cardiorespiratory fitness. 1 MET equals 3.5 ml O_2_/kg/min. An increase in exercise capacity manifested by MET can bring great survival benefits. Small increases in cardiorespiratory fitness (e.g., 1–2 METs) are associated with considerably (10% to 30%) lower adverse cardiovascular event rates (30). CPET will be performed at baseline and the end of the 12-week treatment period. Changes from the baseline will be compared between groups.

The secondary outcomes are as follows:

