1)Composite endpoint events include cardiovascular death, nonfatal myocardial infarction, revascularization, hospitalization for heart failure or unstable angina pectoris, stroke, and other thromboembolic complications. It will be recorded throughout the study. At the end of the 24-week follow-up period, the cumulative incidence of composite endpoint events will be compared between groups.2)Other indicators in CPET: (a) peak oxygen uptake (PeakVO_2_), percentage of predicted PeakVO_2_, oxygen pulse (VO_2_/Heart rate, VO_2_/HR), oxygen uptake related to work rate (ΔVO_2_/ΔWR), Ventilation Aerobic Threshold (VAT). These indicators reflect exercise capacity and cardiac function. (b) The partial pressure of end-tidal carbon dioxide (PETCO_2_), ventilatory equivalent for carbon dioxide slope (VE/VCO_2_ slope). These parameters measure the body's ability to exchange gases. Comparisons between groups will be made on the 12th week after enrollment.3)Seattle Angina Questionnaire (SAQ). SAQ is a valid self-administered scale that estimates five dimensions of health in patients with SCAD: physical limitation, anginal stability, anginal frequency, treatment satisfaction, and disease perception. SAQ will be measured at every visit. Changes from baseline in each dimension of SAQ will be compared between groups.4)TCM syndrome scale (TCMSS). The TCMSS is composed of related symptoms and signs (chest pain, chest tightness, palpitation, shortness of breath, spontaneous sweating, fatigue, distension in the hypochondrium, abdominal distension, heave a deep sigh, impatience and irritability, tongue manifestation, and pulse condition). Scores are assigned according to the severity of items. Measurement will be performed at each visit. The efficacy evaluation criteria are (a). Markedly effective: Clinical symptoms and signs are significantly improved, and syndrome scores are reduced by ≥ 70%. (b) Effective: Clinical symptoms and signs have improved; syndrome scores have been reduced by ≥ 30% and <70%. (c) Invalid: no significant improvement in clinical symptoms and signs, or even aggravation, syndrome score reduction < 30%. (d) Aggravation: The clinical symptoms and signs were aggravated, and the syndrome score decreased < 0.5)12 items of Short Form Health Survey Questionnaire (SF-12), Patient Health Questionnaire-9 (PHQ-9), and Generalized Anxiety Disorder-7 (GAD-7). SF-12, PHQ-9, and GAD-7 will be measured at each visit to evaluate patients' quality of life and current emotions of anxiety and depression, respectively. Changes from the baseline will be compared between groups.6)ST-T segment change in electrocardiogram, improvement of left ventricular ejection fraction (LVEF), as well as left ventricular end-diastolic diameter (LVEDD) in echocardiography will be compared between groups to assess the effect of QTG on myocardial blood supply and cardiac contractile functions at the 12th weeks after enrollment.7)Metabolomics analyses: Blood samples from ten participants per group will be elected randomly for metabolomic analyses. Liquid chromatography-mass spectrometry (LC-MS) and gas chromatography-mass spectrometry (GC–MS) will be adopted to detect the chemical and biological fingerprints, filter effective components, and explore the underlying metabolic pathways and target molecules of QTG for treating SCAD. Concerning the collection of blood samples, participants should fast for at least 8 h. 5 ml blood will be drawn into heparin sodium anticoagulant tubes, centrifuged, and plasma stored in Eppendorf tubes at −80°C.

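### PeakVO2 per kg is the primary METs measurement in other units, yet it is listed as a separate secondary outcome with a differently worded (apparently week-12 value) comparison

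*Protocol article*

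**What the plan says.** All of this is in the Protocol article. The section on primary and secondary outcomes states: "The primary outcome is the improvement of METs in CPET". It gives the conversion "1 MET equals 3.5 ml O_2_/kg/min" and the contrast: "CPET will be performed at baseline and the end of the 12-week treatment period. Changes from the baseline will be compared between groups".

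Item 2 of the secondary outcomes begins with "peak oxygen uptake (PeakVO_2_), percentage of predicted PeakVO_2", followed by oxygen pulse and other gas-exchange measures. The item closes with "Comparisons between groups will be made on the 12th week after enrollment". It gives no units for PeakVO2 and does not say whether the week-12 value or the change is compared.

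The trial schedule (Table 2) has a row "Other indicators in CPET" marked at screening and at week 12, the same two visits as the primary CPET. A baseline therefore exists for every item 2 indicator.

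The Data analysis section names t-tests or rank-sum tests for quantitative data and one threshold, P < 0.05.

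**The concern.** A MET is defined here as a fixed multiple of oxygen uptake per kg. METs reached at peak exercise are then PeakVO2 per kg divided by 3.5, read from the same test in the same patient. Listing PeakVO2 among the other indicators presents one measurement as two outcomes.

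The wording of the comparison differs as well. METs are compared as change from baseline, and secondary items 3 and 5 also speak of changes from baseline. Item 2 names only the week-12 time point, which reads most naturally as a comparison of week-12 values.

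Two problems could follow, depending on which reading is applied:

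- **Contrasts differ.** The trial could report one answer on exercise capacity from METs and another from PeakVO2, although the underlying data are the same, and the text does not say how to reconcile them.
- **Contrasts are the same.** The PeakVO2 result is the METs result repeated, and a reader may take the agreement as corroboration.

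**Working it through.** **1. The plan's own figure.** Inputs from the sample size section: difference 1.38, margin 0.42, SD 1.56, one-sided 2.5%, power 90%, dropout 20%.

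- Effective difference: 1.38 − 0.42 = 0.96.
- Normal approximation: n per arm = 2 × (1.960 + 1.282)² × 1.56² / 0.96² ≈ 55.5, so 56. Then 56/0.8 = 70 per arm, 140 in total.
- Noncentral t: 57 per arm (power 0.903). Then 57/0.8 = 71.25, so 72 per arm and 144 in total.

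The stated 144 is reproduced.

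**2. Same variable, other units.** Multiply the METs inputs by 3.5:

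- difference 1.38 × 3.5 = 4.83 ml/kg/min
- SD 1.56 × 3.5 = 5.46
- margin 0.42 × 3.5 = 1.47

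The standardised effect is unchanged: (4.83 − 1.47)/5.46 = 0.615 = 0.96/1.56. The normal-approximation n is again 56 per arm. A t-test is unaffected by a change of scale. In 20,000 simulated null trials per setting at 60 per arm (75 × 0.8), the P values for change in METs and change in PeakVO2 per kg agreed to about 1e-15. The chance that either was below 0.05 stayed at 0.048 to 0.051.

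**3. Different contrasts.** Suppose METs are tested as change and PeakVO2 as the week-12 value. With equal variances and baseline to week-12 correlation ρ, the covariance of change and week-12 value is σ²(1 − ρ) and the variance of change is 2σ²(1 − ρ). The two test statistics therefore correlate √((1 − ρ)/2). The protocol gives no ρ, so a range is assumed. Under no effect, with each test two-sided at 0.05, the bivariate normal gives:

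| ρ (assumed) | Correlation of statistics | P(either < 0.05) | P(either favourable, 0.025 each) |
|---|---|---|---|
| 0.5 | 0.500 | 0.0907 | 0.0454 |
| 0.7 | 0.387 | 0.0935 | 0.0468 |
| 0.8 | 0.316 | 0.0949 | 0.0475 |
| 0.9 | 0.224 | 0.0962 | 0.0482 |

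Simulation at 60 per arm gave 0.092, 0.093 and 0.093 for ρ = 0.5, 0.7 and 0.8.

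**4. Disagreement.** P(both) = 0.05 + 0.05 − P(either), so P(exactly one) = 2 × P(either) − 0.10. This runs from 0.081 (ρ = 0.5) to 0.092 (ρ = 0.9). Under no effect, most trials with a significant result on either analysis would have it on only one.

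**5. Benchmark.** Two independent tests at 0.05 give 1 − 0.95² = 0.0975. The 0.091 to 0.096 is therefore close to what any second unadjusted test would add. It shows how weakly the two contrasts are tied together and is not an excess peculiar to PeakVO2.

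**The case against.** A reader might infer that PeakVO2 is a second full-alpha test of the primary question that roughly doubles the trial's false-positive rate. The document does not support that. METs are the only primary outcome and the only one used for sizing, and nothing says that a positive PeakVO2 result would count as success. How secondary tests are adjusted is commonly left to an analysis plan that is not shown. The figures above also test against zero and do not model the 0.42 margin.

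A reader might also take it as settled that item 2 compares raw week-12 values. It is not. The sentence fixes a time point only. Item 6 pairs "improvement of left ventricular ejection fraction (LVEF" and related measures with a week-12 comparison, so in this document week-12 timing and change can go together. With a single CPET after baseline, naming week 12 would be natural for a change analysis too. Even a week-12 value comparison would be unbiased under randomisation.

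The exact identity is inferred as well. The outcome section does not say that METs are taken at peak, although the Introduction describes exercise tolerance as maximum capacity and the Quality control section describes a symptom-limited ramp test. Nor is PeakVO2 said to be per kg; in ml/min it would not be an exact rescaling. Percent-predicted PeakVO2 divides by a patient-specific reference, so it is related to the primary but not identical.

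Finally, the two harms exclude each other: identical P values under one reading, discordant answers under the other. That is correct, and they are put forward here only as alternatives.

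These points remove any claim of a proven alpha error. They leave the redundancy under the protocol's own conversion and the open, differently worded contrast.

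**Conclusion.** The point holds as a matter of definition and interpretation. If METs are peak METs and PeakVO2 is per kg, the protocol lists one measurement twice, once as primary and once as secondary, with comparisons worded differently. The primary test's type I error is unchanged.

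If item 2 means week-12 values, at least one of the two analyses is positive under no effect about 9% of the time (0.091 to 0.096), and exactly one is positive 8% to 9% of the time, for assumed ρ of 0.5 to 0.9 and equal variances. If item 2 means change, the second P value repeats the first and carries no further evidence. Either way the text needs to settle which applies. This is an inexpensive improvement to the outcome definitions and does not show the primary analysis to be invalid.

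**What to change.** In the section on primary and secondary outcomes:

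- **Primary.** Define it as change from baseline to week 12 in peak METs, with peak METs = PeakVO2 (ml/kg/min)/3.5.
- **PeakVO2.** Report it in ml/kg/min only as the primary result re-expressed, with estimate and interval multiplied by 3.5. Do not test it separately or cite it as corroboration.
- **Percent-predicted PeakVO2.** It may stay as a secondary indicator, with a note that it shares the primary's numerator.
- **Remaining CPET indicators.** Use the baseline already collected: change from baseline as for METs, preferably with baseline as a covariate. With that adjustment the treatment estimate is the same whether the outcome is the week-12 value or the change, so the ambiguity no longer matters.

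The change is to wording only and needs no extra data or visits. The downside is one fewer secondary outcome with its own P value.

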#### Follow up

After enrollment, all participants will be followed up four times; the first two times at the 4th and 12th weeks after enrollment are study site follow-ups, while the later two times at the 12th and 24th weeks after treatment are telephone follow-ups.

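### The full TCM syndrome scale cannot be scored as described at the two telephone visits, and its Invalid category contains all of Aggravation

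*Protocol article*

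**What the plan says.** In the protocol article, item 4 under The primary and secondary outcomes defines the TCM syndrome scale. It names ten symptoms and then two signs, and fixes the timing: "tongue manifestation, and pulse condition). Scores are assigned according to the severity of items. Measurement will be performed at each visit". Table 2 (Trial schedule) agrees, with the scale marked at V1 to V5.

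The Follow up section sets the mode of contact for the four visits after enrolment. V2 and V3 take place at the centre. For V4 (week 24) and V5 (week 36), as Table 2 numbers them, the section states that "the later two times at the 12th and 24th weeks after treatment are telephone follow-ups".

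Item 4 also sets four efficacy categories on the percentage reduction in score:
- Markedly effective: "Clinical symptoms and signs are significantly improved, and syndrome scores are reduced by ≥ 70" per cent.
- Effective: "syndrome scores have been reduced by ≥ 30% and <70" per cent.
- Invalid: "no significant improvement in clinical symptoms and signs, or even aggravation, syndrome score reduction < 30" per cent.
- Aggravation: symptoms and signs worse, with a score reduction below 0.

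The Data analysis section names last observation carried forward (LOCF) as the method for missing outcome data. The article gives no item weights, no reduced form of the scale and no scoring rule for telephone visits.

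**The concern.** Two of the twelve listed items are signs that an assessor examines. Pulse condition in particular needs contact with the patient. A telephone call cannot supply it, so the total defined in item 4 does not exist at V4 and V5 for any patient in either arm. A percentage reduction from a 12-item baseline then has no matching numerator.

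The 24 weeks after treatment are the trial's only off-treatment period, and the scale measures the syndrome that defines eligibility. What is at stake is whether a follow-up score describes the patient at week 24 or 36, or partly repeats the end of treatment.

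The second defect is separate. The four categories read as a classification, but the third has no lower bound and expressly takes in worsening, which is also the fourth.

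**Working it through.** **Step 1. Mode of visit against content of scale.**

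| Visit | Week | Mode (Follow up section; V1 holds the baseline examinations) | Scale marked in Table 2 | Tongue and pulse obtainable as described |
|---|---|---|---|---|
| V1 | baseline | site | yes | yes |
| V2 | 4 | site | yes | yes |
| V3 | 12 | site | yes | yes |
| V4 | 24 | telephone | yes | no |
| V5 | 36 | telephone | yes | no |

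In the same table, vital signs, laboratory tests, electrocardiogram, echocardiography and CPET all stop at V3. The schedule drops the other hands-on measurements from the telephone visits but keeps this scale unchanged.

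**Step 2. What the missing signs can do to the score.** The article states no figure for this scale, so there is none to reproduce. Let w be the share of a patient's baseline score that comes from tongue and pulse. This is an assumption; equal item weights and equal baseline severity would give w = 2/12. Let r be the true reduction, the same in all items.

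- Signs scored zero: apparent reduction = r(1 − w) + w, so the true reduction needed to reach 30% is (0.30 − w)/(1 − w).
- Signs held at their baseline value: apparent reduction = r(1 − w), so the true reduction needed is 0.30/(1 − w).

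| w | Needed for Effective, signs zero | Needed for Effective, signs at baseline |
|---|---|---|
| 5% | 0.25/0.95 = 26.3% | 0.30/0.95 = 31.6% |
| 10% | 0.20/0.90 = 22.2% | 0.30/0.90 = 33.3% |
| 2/12 | 0.1333/0.8333 = 16.0% | 0.30/0.8333 = 36.0% |
| 25% | 0.05/0.75 = 6.7% | 0.30/0.75 = 40.0% |

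Neither rule is in the article. The table shows only that the effective cut-off moves either way with the handling chosen.

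**Step 3. The rule that is stated, LOCF.** Take a patient with a 70% reduction in every item at week 12 who is fully back to baseline at week 24. The true reduction is 0%.

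- LOCF on the incomplete total: week 12 is repeated, 70%, which meets the score criterion for Markedly effective.
- LOCF on the two items only: 0 × (1 − w) + 0.70w = 3.5% (w = 5%), 7.0% (10%), 11.7% (2/12) or 17.5% (25%).

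The article does not say at which level the rule applies. On the total, weeks 24 and 36 carry no new information. On the items, week-12 signs are mixed with later symptoms. In both cases on-treatment values replace data that were never going to be collected.

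**Step 4. The category rules.** Applied to a grid of percentage reductions:

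| Reduction | Categories met |
|---|---|
| 90, 70 | Markedly effective only |
| 69.9, 50, 30 | Effective only |
| 29.9, 10, 0 | Invalid only |
| −0.1, −20 | Invalid and Aggravation |

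The overlap is confined to reductions below 0. A count of patients with a reduction of at least 30% is the same whichever way it is resolved.

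**Step 5. Reach.** The sample size rests on METs alone: difference net of margin 1.38 − 0.42 = 0.96, SD 1.56, one-sided 2.5%, 90% power. The noncentral t calculation gives 57 per arm (power 0.903); 57/0.8 = 71.25, rounded up to 72 per arm, 144 in total, as stated. Nothing here touches it.

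**The case against.** The strongest reply is that this is one secondary outcome among many, affected at two visits only. Site scores at baseline, week 4 and week 12 are sound. With blinding, whatever handling is chosen applies to both arms alike, and no between-group bias has been shown. The article gives no weights, so any single magnitude is invented. It does not say that the four categories are tabulated at V4 and V5, and it defines no overall response rate. A lower bound on Invalid settles the overlap in one line.

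All of that stands, and it limits the point. A reader might infer that follow-up response rates will be inflated, or that response rates in general will be wrong. The documents support neither. Inflation follows from scoring the signs zero, which is nowhere stated; holding them at baseline deflates the response instead. The category overlap lies entirely among patients below the 30% cut-off and cannot change a rate based on that cut-off.

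What the reply does not remove is the conflict itself. An article may leave scoring detail to a fuller document. Here, though, the current text states the visit mode, the schedule and the scale's content, and the three do not fit together. Equal handling in both arms does not make a carried-forward week-12 value an off-treatment measurement.

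**Conclusion.** The point holds as an internal inconsistency in a secondary outcome. As described, the 12-item scale cannot be scored at weeks 24 and 36. Under the stated LOCF rule, week-12 on-treatment values would stand in for data missing by design, so the follow-up scores would not be comparable with baseline. No direction or size can be fixed: the ranges shown rest on an assumed 5% to 25% share for the two signs and on handling rules chosen for illustration. The Invalid and Aggravation counts are ambiguous for every worsened patient, at any visit where the categories are used. Apart from that overlap, V1 to V3 scores are unaffected. The primary outcome and the sample size are untouched.

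**What to change.** Reconcile the Follow up section, Table 2 and item 4 of the outcomes:

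1. Limit the full scale, and the categories built on it, to the site visits V1 to V3.
2. At V4 and V5, collect a prespecified ten-symptom telephone subscore and compare it with the same ten-symptom subscore at baseline.
3. State that tongue and pulse are not carried forward to V4 or V5.
4. Define Invalid as a reduction of at least 0% and below 30%, leaving reductions below 0% to Aggravation.

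Making V4 and V5 site visits would also resolve the conflict, but with a larger burden on patients and centres. The change proposed here needs only edits to the schedule table and wording. It gives up an off-treatment tongue and pulse score, which could not be obtained by telephone as described.

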
#### Safety assessment and adverse events report

This study will evaluate safety by monitoring adverse events (AEs), serious adverse events (SAEs), withdrawals, or treatment alterations due to AEs. In addition, laboratory tests (blood routine, urine analysis, stool for routine and occult blood test, liver and renal function, blood lipid, and blood coagulation function) and vital signs will be conducted to assess the safety of QTG. Safety evaluation will be performed at baseline, the fourth week during treatment, and at the end of treatment. All SAEs will be reported to the ethics committee. The severity of AEs will be graded using CTCAE version 5.0. When subjects suffer from trial-related personal injury, appropriate treatment measures will be taken timely to ensure their safety. Subject compensation claims will also be properly handled.

#### Data collection and management

A paper CRF is used for data collection, and the laboratory and inspection results should be accurately, completely, and normatively recorded on the CRF promptly. After the clinical trial, CRFs will be checked by the clinical monitor for data integrity and then handed over to the data administrator for entry. Electronic CRF in the electronic data capture (EDC) system is designed strictly adhere to CRF's research protocol and content. All data will be input electronically at Xiyuan Hospital when the last patient is followed up. Two groups of trained researchers will conduct independent double data entry to ensure accuracy. The database support data format, valid values, and range checks. Questions proposed by data administrators will be sent to investigators by monitors in the form of data query reports. Researchers will respond by checking the original material. Data entry clerks will update the database according to the reply contents on the query reports. Adverse events, medical diagnoses, concomitant medications, past medical history, etc., collected from the CRF will be coded in terms from the Medical Dictionary for Regulatory Activities (MedDRA). After the data cleaning, a blind review meeting will be held, and the database will be locked. All paper files related to the study data will be stored in numerical order and kept in locked cabinets. Access to the study data will be restricted. Participant files will be maintained in storage for five years after completing the study.

